### Title: Improving stroke prevention in atrial fibrillation.

**Background**

Patients with atrial fibrillation (AF) are at high risk for stroke, with up to a fivefold risk compared to patients without AF ([1](#_ENREF_1)). Apart from the increased risk, stroke severity is increased ([2](#_ENREF_2)). Therefore, patients with AF need to be treated with antithrombotic medication to reduce stroke risk. Oral anticoagulation (OAC), such as warfarin and the new oral anticoagulants (e.g. dabigatran), reduces the risk of stroke by 60%, and antiplatelet drugs by 20% ([3](#_ENREF_3), [4](#_ENREF_4)). Because OAC increases the risk of bleeding, not every patient is eligible for this treatment, as there are patients with a pre-existing increased risk of bleeding. Guidelines have been developed to help the physician decide which treatment is appropriate for a patient. These guidelines incorporate contraindications for OAC, and stroke risk stratification schemes to balance risks and benefits. Estimates of current adherence to stroke risk guidelines in the prevention of stroke in patients with atrial fibrillation is about 50% internationally, leading to both over- and under-treatment. This is true for both primary and secondary care ([5-7](#_ENREF_5)). Research on the reasons for these low adherence rates is lacking. We hypothesize that patient preference and medical context, lack of time and lack of overview are important drivers in this process. These are reasons that have been shown to influence guideline adherence in general in previous studies ([8](#_ENREF_8)). More insight into the reasons physicians state for non-adherence could prove valuable for future research and guideline development.

The aim of this study is to investigate the effect of a clinical decision support system (CDSS) on adherence to the guideline that recommends antithrombotic treatment for stroke prevention for patients with atrial fibrillation. Clinical decision support systems have proven to be effective interventions for improving various healthcare processes ([9](#_ENREF_9), [10](#_ENREF_10)). However, evidence for clinical improvement is sparse ([9](#_ENREF_9), [11](#_ENREF_11)). We hope to expand the current body of evidence for the effectiveness of CDSS with findings of increased guideline adherence and, in follow-up projects, better clinical outcomes. Furthermore, not all instances of non-adherence might be undesirable. Physicians may have good clinical reasons (e.g. comorbidity, social environment) to deviate from recommended treatment. Therefore, the second objective of this study is to study reasons for deviation. Lastly, we would like to evaluate whether the requirement for justification influences response to a clinical decision support system.

**Design**

This study will be a cluster randomized controlled trial. Randomization at the patient level was considered, but deemed inapplicable due to the fact that one GP would have patients in both the control and intervention groups, thus leading to possible contamination bias. Randomization at the GP level was not possible, because most GPs work in group-practices and share patients, which would lead to a GP in the control group reading the reports of another GP that received the intervention. This would also lead to contamination bias. It was therefore decided to randomize on the GP cluster level, where GPs treating the same patients will be regarded as a randomization unit (usually 2 or 3 GPs).

GPs will be allocated into three groups:
1. Will receive no messages (control group)
2. Will receive messages that can be ignored without justification (intervention 1)
3. Will receive messages that can only be ignored with justification (intervention 2)

**Intervention**

We have developed a plugin (an extra piece of software that is not an integral part of the main system) for a single GP electronic health records system (EHRS). The CDSS plugin can be classified as active (it does not wait to be asked), non-interruptive (does not interrupt the workflow), and critiquing (provides feedback based on the current treatment scheme). The basic functionality of this decision support system is based on detecting relevant events based on triggers, evaluating the events and responding to them. Several trigger points in the GPs’ EHR have been designed. Trigger points are events that may occur in a system that then trigger an action(for instance “Closing a record”=>“send data to the server”). These triggers are:

- opening a patient's electronic medical record on the computer
- adding laboratory data (e.g. a new glomerular filtration rate (GFR))
- changing medication (e.g. prescribing aspirin)
- updating the patient's problem list (e.g. registering a diagnosis of atrial fibrillation)

Whenever a trigger is activated, information from the on-screen medical record (the medical record that is currently opened on the GP's screen) is sent to a remote server via a secure Internet connection. This information consists of recent laboratory data (12 months), active medication and a list of the patient's diagnoses. On the remote server a clinical rule engine (CRE) evaluates the provided information using the computerized decision rule (see decision rule). The evaluation of the decision rule may lead to a response in the form of a message. This message is formatted as an XML (a file format designed to exchange data) document and sent to the CDSS plugin that has been installed on the GP’s computer. The plugin reads the XML file and evaluates the contents. It extracts the message title and displays part of the title in a thin sidebar that is attached to the right side of the GP’s screen. The GP can move the mouse cursor over the sidebar to display the full message title. He or she can then choose to either ignore the message by clicking on the “ignore” button, or open the message by clicking anywhere on the message title. When the message is opened, a report is shown that displays the complete message, as well as the findings that have led to the message, and a clickable link to online background information. Upon first appearance, the message title is displayed with a red background in the sidebar, indicating the message is new. If the GP does not interact with the message, the background will become orange the next time the GP opens the electronic medical record, indicating the message has been shown before but not dealt with yet. When the GP changes the treatment plan according to the guideline, the background will turn green and the message title will be updated. This can happen without opening the message, i.e. the GP might already know that he or she needs to change the treatment plan and doing so will also result in a green background and updated message, without having to interact with the CDSS plugin.

It is important to note that by using this procedure, real-time feedback to the GP is provided. This means that the GP will see a direct effect of every relevant action he or she performs on the screen.

When analysing baseline data to determine the current proportion of correctly treated patients, we found that recorded diagnoses of stroke were often incomplete or inaccurate. Therefore, a single question was added to the messages of the rule engine, which asks the GP for the exact type of stroke if/when the International Classification of Primary Care (ICPC) ([12](#_ENREF_12)) code for stroke (K90) is found on the patient's diagnoses list. The following options will be presented to the GP: subarachnoid haemorrhage (K90.01), haemorrhagic stroke (K90.02) and ischemic stroke (K90.03). Once the question is answered, the response is saved for future use and sent to the clinical rule engine, where the entire decision rule can be evaluated.

GPs who are allocated into the third group (intervention 2) will not be able to ignore a message without providing justification. The GP is presented with several predefined options and a free text field, which will allow him or her to enter other explanations. The GP cannot continue without answering this question. When the GP tries to close the on-screen medical record without providing a reason for deviating from the advice, he or she is reminded once more of the message and asked to respond. An independent adjudication committee will value the legitimacy of the reasons provided to deviate from the advised treatment, and will contact GPs when necessary.

**Decision rule**

The computerized decision rule is based on the Dutch GP guideline for atrial fibrillation authored by the Dutch College of General Practitioners ([13](#_ENREF_13)). This guideline uses the CHADS2 score: A commonly used stroke risk stratification scheme, which is calculated by assigning 1 point each for the presence of congestive heart failure, hypertension, age 75 years or older, and diabetes mellitus; and by assigning 2 points each for history of stroke or transient ischaemic attack (TIA)([14](#_ENREF_14)).

The decision process consists of two phases:

1. The rule engine uses the decision rule to determine the recommended treatment.
2. The rule engine compares the actual treatment to the recommended treatment and generates the message according to the result.

The first phase is a two-step procedure:

1. Determine whether contraindications for OAC are present. If this is the case, antiplatelet drugs are the preferred treatment.
2. Calculate the CHADS2 score. For scores of one and lower, the preferred treatment is antiplatelet drugs; for scores of two and higher, the preferred treatment is OAC.

In the second phase, the recommended treatment is compared to the actual treatment. A message is generated using this information, e.g. “It is advised to stop OAC and start antiplatelet drugs, due to the fact that this patient has a CHADS2 score of 1.” There are a total of 11 unique messages.

**Baseline measurements**

Baseline measurements will be performed to determine the current proportion of patients with AF who are treated in accordance with the guideline. These data will be gathered by automatically evaluating the decision rule on all patients in an anonymized copy of the GP’s EHR databases before the start of the study.

**Regulatory aspects**

The medical ethics committee of the AMC deemed this study exempt from ethical approval because the intervention is a way of providing valid medical information to GPs and does not change medical treatment or use invasive procedures. Furthermore, only anonymized patient data is used for analysis.

Every practice has provided written consent to participate in this study via a designated GP representative.

This trial is registered with the Dutch trial register under number: 3570.

**Data collection**

Whenever a message is shown, clicked, or ignored in the CDSS plugin, this event is stored in a database along with the current time and date. This will allow us to analyse the way the system is used by the GPs and will inform us about possible improvements that can be made. The responses GPs give to the questions about the type of stroke and the reason to ignore the message, if any, are saved inside the XML document and sent back to the remote server where the document is stored. During the study, these XML files will be opened and the responses will be extracted. To calculate adherence rates we use anonymized patient data (disease list, medication, GP contacts, lab data), which are extracted directly from the GP’s EHR databases.

**Population**

We will include GP practices in the Netherlands that use the EHR for which the plugin was developed. Initially, we will include every GP practice (18 clusters of GPs, with a total of 35 GPs) that is part of the GAZO (a network of GP practices in Amsterdam Southeast). Decision support messages will be shown for every patient with atrial fibrillation (both new and existing patients) who visits the GP in his or her practice.

**Sample size and analysis**

A power analysis showed that 300 patients are needed for a power of 0.8 when assuming a base adherence of 50%, an absolute effect size of 10% for intervention group 2 and 20% for intervention group 3, with a test significance level of 0.05. Because GPs are clustered for randomization, a correction for these clustering effects was introduced. For the cluster correction analysis, an intra-class correlation of .1 was assumed, based on studies using similar clustering ([15](#_ENREF_15)). This resulted in a required sample size of approximately 500 patients to result in an effective sample size of 300.

When data collection has been concluded, differences in adherence percentages will be calculated per GP cluster. A chi-square test will be used to compare the differences in the three groups.

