**Effect size and reasons for non-adherence**
We expect a 10% and 20% absolute effect size in intervention groups A and B, respectively. We hypothesize that the main reason for non-adherence is that there are too many parameters in this guideline to be evaluated effectively during a 10-minute visit. If a patient develops diabetes and reaches the age of 75, that has an impact on multiple guidelines. It is virtually impossible to know every guideline by heart, as there are currently one hundred Dutch GP guidelines, 10% of which are revised every year. Hence, the GP will often not be aware that the patient in fact needs to receive OAC instead of aspirin due to the fact that his or her CHADS2 score increased by two points.

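### With equal groups, 300 independent patients give the named three-group chi-square test a power of about 0.74, not 0.8, and the 10-point contrasts only about 0.3

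*Protocol*

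**What the plan says.** The Design section sets up a control group (group 1), messages that can be ignored freely (group 2, intervention 1) and messages that can be ignored only with a justification (group 3, intervention 2). It gives no allocation ratio.

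Under Sample size and analysis the protocol states: "A power analysis showed that 300 patients are needed for a power of 0.8 when assuming a base adherence of 50" per cent. The other inputs are "an absolute effect size of 10% for intervention group 2 and 20% for intervention group 3", "with a test significance level of 0.05". The same effects return under Effect size and reasons for non-adherence: "We expect a 10% and 20% absolute effect size in intervention groups A and B, respectively".

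Clustering is brought in afterwards: about 500 patients are to be recruited so that the effective number is 300. The 300 is therefore a total over the three groups, before cluster inflation.

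The analysis is given as: "A chi-square test will be used to compare the differences in the three groups". The Outcomes section makes the difference in adherence between groups 1, 2 and 3 the primary outcome. The Background adds a further aim: "Lastly, we would like to evaluate whether the requirement for justification influences response to a clinical decision support system".

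**The concern.** The sentence gives one power figure for a configuration with two different effects, and does not say which comparison the figure belongs to. The natural reading is that it belongs to the only test named, the three-group chi-square. That can be checked directly, and the figure does not come out.

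The second issue is what a reader does with the 0.8. Because the 10-point effect stands among the inputs, a reader may assume that such an effect is well covered. Intervention 1 against control is a 10-point contrast. So is intervention 2 against intervention 1, the contrast that bears on the justification aim as far as that aim is judged on adherence. If power for these is low, a non-significant result is likely even when the assumed effects are real, and the stated 0.8 would invite reading it as no effect.

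**Working it through.** **Inputs.** From Sample size and analysis: adherence 0.50, 0.60 and 0.70; alpha 0.05; total N = 300; target power 0.80. My assumptions: equal groups (100 each), two-sided pairwise tests, independent patients, and the chi-square read as the 2-df test of three proportions.

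**1. Reproducing the 300.** For two proportions with difference d and mean p̄, using the pooled variance under the null:

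n per arm = [1.96·√(2p̄(1−p̄)) + 0.8416·√(p₁(1−p₁) + p₂(1−p₂))]² / d²

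- 50 v 70%: (1.96 × 0.6928 + 0.8416 × 0.6782)² / 0.04 = 3.720 / 0.04, so 93 per arm, or 3 × 93 = 279 in total. With continuity correction it is 103 per arm, or 309 in total.
- 1-df linear trend over the three groups: 283 in total.

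So 300 is close to what the single 20-point contrast or a trend test needs.

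**2. The named test.** Mean adherence is 0.60. The effect size is

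w² = [(0.01 + 0 + 0.01)/3] / (0.60 × 0.40) = 0.006667 / 0.24 = 0.02778

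The noncentrality at N = 300 is 300 × 0.02778 = 8.33. Against the 2-df critical value of 5.99, power is 0.736. A simulation of 400,000 trials gives 0.744, and two other forms of the noncentrality give 0.744 and 0.749, so the shortfall does not come from the approximation. Power 0.80 needs N = 347 (noncentrality 9.64), or 348 with equal groups of 116.

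The trend test has the same noncentrality, because the three rates lie on a line, but it uses 1 df: √8.33 − 1.96 = 0.927, power 0.82.

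**3. The pairwise contrasts at 100 per arm.** Power = Φ[(d − 1.96·SE₀)/SE₁], where SE₀ is the pooled and SE₁ the unpooled standard error.

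| Contrast | SE₀ | SE₁ | Φ argument | Power | n per arm for 0.80 |
|---|---|---|---|---|---|
| Intervention 1 v control, 50 v 60% | 0.0704 | 0.0700 | −0.541 | 0.29 | 388 |
| Intervention 2 v intervention 1, 60 v 70% | 0.0675 | 0.0671 | −0.480 | 0.32 | 356 |
| Intervention 2 v control, 50 v 70% | 0.0693 | 0.0678 | 0.947 | 0.83 | 93 |

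Exact calculation gives 0.31, 0.32 and 0.83. The 10-point contrasts would need 388/100 = 3.9 and 356/100 = 3.6 times the planned 100 per arm. Even if all 500 recruited patients were independent (about 167 per arm), their power would be only 0.45 and 0.48.

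**4. Sensitivity.**
- One-sided testing raises the 10-point contrasts to 0.41 and 0.44, still far from 0.8.
- With a fraction a of patients in each outer group and 1 − 2a in the middle group, the noncentrality at N = 300 is 300 × 2a × 0.01/0.24 = 25a. Equal groups give 8.33. Power 0.80 needs about 9.63, so a ≈ 0.385, a split of about 38.5/23/38.5.

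**The case against.** **The gap for the named test is modest and rests on equal groups.** Both are true: 0.74 against 0.80, or 347 patients against 300. A smaller middle group could close the gap, but the protocol announces no such split, and equal groups are the natural reading of a three-group design without a stated ratio.

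**The protocol does not claim 0.8 for every contrast.** This stands. A reader might infer from the two listed effects that each 10-point comparison has been given a power of 0.8. The text offers a single figure for the whole 50/60/70 configuration and names no pairwise test. The effect of decision support can also be read from intervention 2 against control (0.83), though that combines the messages with the justification requirement, or from both interventions pooled against control (0.70). The low power of the 10-point contrasts is thus something the section leaves undisclosed, not a second arithmetic error.

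**A three-group test is a legitimate first step.** This also stands. A reader might infer that the chi-square is the wrong test because it does not say which groups differ. With three groups, an overall test followed by pairwise tests is an accepted approach, and follow-up contrasts are commonly left to the statistical analysis plan, which is not shown. The documents give no ground for requiring a different testing scheme.

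**The 300 may mean patients per arm.** The text does not support this, since about 500 patients are said to yield an effective 300. Even at 300 per arm, two-sided power for the 10-point contrasts would be 0.69 and 0.73.

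**Clustering may make power lower still.** A reader might extend the argument to power after clustering. That depends on the final number and size of clusters, and the Population section includes its 18 clusters only as a start. Whether 500 patients deliver an effective 300 is a separate point, and nothing here relies on it.

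**Conclusion.** The stated power does not match the stated test. With equal allocation, independent patients and the protocol's own rates and alpha, the three-group chi-square has power of about 0.74 at N = 300. The 0.8 is met only by intervention 2 against control or by a trend test. The former probably explains where the number came from, but it does not make the sentence true for the test the section names.

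The practical weight lies with the 10-point contrasts. If the assumed effects are real, each would come out non-significant about seven times in ten (1 − 0.29 = 0.71 and 1 − 0.32 = 0.68), before any loss to clustering. This is not a matter for the unseen analysis plan, because the protocol itself fixes the figure, its inputs and the test. It is a misstatement of power to be put right, and it does not by itself show that the design cannot detect the 20-point effect.

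**What to change.** Rewrite the power statement under Sample size and analysis to:

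- state the allocation ratio and the comparison to which the 0.8 refers;
- give the power for 300 independent patients in equal groups: about 0.74 for the three-group test, about 0.83 for intervention 2 against control, and about 0.3 for each 10-point contrast;
- say that the 10-point contrasts will be reported as estimates with cluster-adjusted confidence intervals, and that a non-significant result for them will not be taken as evidence of no effect.

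The three-group test can stay. If the 0.8 is meant to apply to it, the number before cluster correction becomes 348 (116 per group) in place of 300.

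The restatement costs only protocol wording. Its drawback is that the declared power becomes less favourable, most visibly for intervention 1 and for the justification question.

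### The stated 300 patients for power 0.8 does not match the three-group chi-square test the protocol names: with equal groups that test has power of about 0.74 at 300 and needs about 347

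*Protocol*

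**What the plan says.** Under Sample size and analysis the protocol gives the size before any allowance for clustering: "A power analysis showed that 300 patients are needed for a power of 0.8 when assuming a base adherence of 50"%. The gains assumed over control are 10 points in the first intervention group and 20 points in the second, and alpha is 0.05. These 300 patients then become the effective sample size that about 500 recruited patients are meant to deliver, at an intra-class correlation of 0.1.

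The next paragraph of that section names the analysis: "A chi-square test will be used to compare the differences in the three groups". No other confirmatory test appears. The Outcomes section defines the primary outcome as the difference in adherence between groups 1, 2 and 3 and singles out no pair.

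The discussion part, under Effect size and reasons for non-adherence, repeats the effects: "We expect a 10% and 20% absolute effect size in intervention groups A and B, respectively". I read A and B there as groups 2 and 3 of the Design section. That section states "GPs will be allocated into three groups" and gives no allocation ratio.

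The protocol does not say which test or contrast the power analysis used, or whether it was one- or two-sided.

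**The concern.** Effects, alpha, power, size and test all stand in one section, so they can be checked against each other. A power of 0.8 placed beside a single named test will be taken as the power of that test.

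If it is not, two things follow. A non-significant overall result would be read as coming from a trial with 80% power when the planned test had less. And the 300 is the target of the cluster correction, so the mismatch enters before clustering and is carried into the figure of about 500.

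The 10-point effect adds to this. It is listed among the assumptions behind the 0.8, and the Background section makes the effect of required justification (60% versus 70%) one of the trial's own questions. The protocol gives no sign of how little power that comparison has.

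**Working it through.** **Inputs from the protocol.** Adherence 0.50, 0.60 and 0.70 in groups 1, 2 and 3; alpha 0.05; power 0.8; N = 300 before clustering; chi-square test over three groups (Sample size and analysis).

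**Assumptions.** Equal groups (100 each at N = 300), independent patients, and a Pearson chi-square on the patient-level 2 × 3 table, so 2 df.

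**1. Trying to reproduce the 300 with the named test.**
- Mean adherence = (0.50 + 0.60 + 0.70)/3 = 0.60.
- w² = mean of (pᵢ − 0.60)² divided by (0.60 × 0.40) = [(0.01 + 0 + 0.01)/3]/0.24 = 0.02778.
- Noncentrality λ = N × w². At N = 300, λ = 8.33.
- Power = P(noncentral χ² with 2 df and λ = 8.33 exceeds the 5% critical value) = **0.736**.
- The first N that reaches 0.80 is **347** (λ = 9.64), and 347/300 = 1.16.

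The choice of approximation does not close the gap. Simulation of 400,000 trials at 100 per group gives 0.744, a likelihood-ratio version 0.747, an arcsine version 0.744 and an unpooled Wald version 0.757. Simulated power is 0.803 at 115 per group and 0.806 at 116.

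**2. What does give about 300.** None of these comparisons is planned in the protocol.

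| Comparison | N over three arms for 0.80 | Power at 300 |
|---|---|---|
| 50% vs 70%, two-sided 0.05 | 3 × 93 = 279 | 0.828 |
| Same, with continuity correction | 3 × 103 = 309 | – |
| Linear trend, 1 df | 283 | 0.823 |
| Control vs pooled interventions (50% vs 65%, 1:2), one-sided 0.05 | 300 | 0.803 |

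The last comparison done two-sided needs 378 and has power 0.70 at 300.

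**3. The 10-point contrasts at 100 per group, two-sided 0.05, no multiplicity adjustment.** Power = Φ{[d√n − 1.96√(2p̄(1 − p̄))]/√(p₁(1 − p₁) + p₂(1 − p₂))}, with d = 0.10 and n = 100.
- 50% vs 60%, p̄ = 0.55: (1 − 1.96√0.495)/√0.49 = −0.54, power **0.29**; 388 per group needed for 0.80.
- 60% vs 70%, p̄ = 0.65: (1 − 1.96√0.455)/√0.45 = −0.48, power **0.32**; 356 per group needed for 0.80.

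Over one- and two-sided tests with alpha from 0.0167 to 0.05, power for these two contrasts runs from 0.16 to 0.44 and never comes near 0.8.

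**The case against.** The strongest reply is that the 300 may be sound arithmetic for a comparison the protocol does not name. The chi-square sentence stands in the paragraph on analysis, not in the one on power, and the table shows several calculations that land near 300. This stands. A reader might infer that the 300 is simply a miscalculation, but the document does not support that, because the test behind the figure is not given. It does not remove the mismatch: if another comparison was powered, the protocol plans one test and quotes the power of another.

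Equal allocation is also an assumption. With a thin middle group the 2-df test does better: 18 equal clusters split 7:4:7 would reach 0.80 at about 298. Nothing suggests such a split, and equal groups are the natural reading, but the ratio should be stated. Likewise, the protocol speaks of differences calculated per GP cluster, so a patient-level 2 × 3 table is a fair reading and not the only one.

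A reader might also infer that the protocol promises 0.8 for each 10-point difference. It does not say so. The 10 and 20 points are joint assumptions, the primary outcome names no pair, and pairwise tests may be set out in an analysis plan not shown. The low power of these contrasts is therefore something to disclose, not an error in a stated figure.

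Finally, the gap of 0.74 against 0.80 is modest. That is fair, and it is why rewording is enough.

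**Conclusion.** The concern holds as a mismatch between the stated size and the only named test. With equal groups, independent patients and adherence of 50%, 60% and 70%, the three-group chi-square test has power of about 0.74 at 300, not 0.8, and needs about 347. Each 10-point contrast has power of about 0.3. These figures also suppose that an effective size of 300 is reached, which is a separate question.

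It would be tempting to scale the recruitment target by the protocol's ratio of 500 to 300. The document does not support this. With a limited number of clusters, inflation is not a fixed ratio, and the protocol's own inputs do not give that one: 500 patients in the 18 initial clusters are 27.8 per cluster, so the design effect is 1 + 0.1 × 26.8 = 3.68 and the effective size about 136 (equal clusters; more may join later).

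**What to change.** In Sample size and analysis:

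1. State which test, contrast, sidedness and allocation ratio the 300 and the 0.8 refer to.
2. If they refer to the three-group chi-square test with equal groups, restate power as about 0.74 at an effective 300, or give 347 as the effective size for 0.80.
3. If they refer to another comparison, say that 0.8 applies to that comparison only and that the planned three-group test has about 0.74.
4. Disclose that 50% versus 60% and 60% versus 70% each have power of about 0.3 at an effective 300, and that the second is the justification question raised in the Background.
5. Redo the cluster correction from the restated figure, using the actual number of clusters.

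The cost is the rewording of one paragraph and a less favourable stated power. No extra enrolment and no change of design or analysis is asked for.

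### The protocol's step from 500 patients to an effective 300 does not fit its only stated cluster count: with 18 clusters at an ICC of 0.1 the effective sample size is about 136 and cannot exceed 180

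*Protocol*

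**What the plan says.** The section Sample size and analysis starts from an uncorrected calculation: "A power analysis showed that 300 patients are needed for a power of 0.8", under three assumptions:

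- control adherence: "assuming a base adherence of 50" per cent
- effects: "an absolute effect size of 10% for intervention group 2 and 20% for intervention group 3"
- type I error: "with a test significance level of 0.05"

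It then corrects for clustering. For this, "an intra-class correlation of .1 was assumed", and "This resulted in a required sample size of approximately 500 patients to result in an effective sample size of 300". The section gives neither the number of clusters nor the cluster size used in the correction. It names a chi-square test across the three groups.

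The number of clusters appears only under Population: "Initially, we will include every GP practice (18 clusters of GPs, with a total of 35 GPs". Under Design, the unit of randomisation is the cluster and not the single GP: "It was therefore decided to randomize on the GP cluster level, where GPs treating the same patients will be regarded as a randomization unit".

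**The concern.** At a given ICC, the design effect depends on the average cluster size, and so on how many clusters the patients are spread over. Moving from 300 to 500 implies a design effect of 1.67, which at an ICC of 0.1 means small clusters and many of them. The 18 clusters under Population would each hold several times as many patients, and the correction should then be far larger.

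The primary comparison of adherence between the three groups rests on this sample size. If the trial runs in 18 clusters, it would be presented as having 80% power for the effects it expects when it is more likely than not to miss them. A null result could then be read as failure of the decision support system when the design could hardly have shown the expected effect.

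**Working it through.** **Inputs from the protocol.** N = 500, target effective size 300, ICC = 0.1, power 0.8, alpha 0.05 and adherence 50/60/70% (Sample size and analysis); 18 clusters and 35 GPs (Population); cluster as randomisation unit (Design).

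**Assumptions added here.** Equal cluster sizes, 1:1:1 allocation (six clusters per group), two-sided alpha, and a comparison of adherence at the end without use of baseline.

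**1. The uncorrected 300.** It reproduces within 3% as 50% versus 70% with continuity correction: 3 × 103 = 309. Nearby readings are 279 (the same comparison, uncorrected), 283 (1-df trend) and 347 (three-group chi-square, 2 df).

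**2. What 500 to 300 implies.** With design effect DE = 1 + (m − 1) × ICC, where m is the mean cluster size:
- DE = 500/300 = 1.667
- m = 1 + 0.667/0.1 = 7.67
- clusters = 500/7.67 = 65.2

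**3. What 18 clusters give.**
- m = 500/18 = 27.8
- DE = 1 + 26.8 × 0.1 = 3.68
- effective N = 500/3.68 = 136
- as N grows, effective N approaches 18/0.1 = 180, so 300 is out of reach with any number of patients
- for 500 patients in 18 clusters to give 300, the ICC would have to be 0.667/26.8 = 0.025

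**4. Other routes to the protocol's figure.**
- The 35 GPs as clusters: m = 14.3, DE = 2.33, effective N = 215.
- m taken from the uninflated 300 over 18 clusters: 16.7, DE = 2.57, N = 770.
- m taken from the uninflated 300 over 35 GPs: 8.57, DE = 1.757, N = 527. This comes closest to 500, but it uses the wrong unit and a cluster size that no longer applies once N is inflated.

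None reproduces 500 within 3%, and neither effective size (136 or 215) is near 300.

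**5. Power.** For 50/60/70% in equal groups, w² = [(0.1² + 0 + 0.1²)/3]/(0.6 × 0.4) = 0.0278. The noncentrality is N × w²: 8.33 at 300, 3.78 at 136 and 5.0 at 180.

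| Test | Effective N 300 | Effective N 136 |
|---|---|---|
| Three-group chi-square, 2 df | 0.74 | 0.39 |
| Cluster-level F, 2 and 15 df | – | 0.33 |
| 1-df trend | 0.82 | 0.49 |
| 50% vs 70%, uncorrected | 0.83 | 0.49 |
| 50% vs 70%, continuity-corrected | 0.79 | 0.40 |

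At the ceiling of 180, power is 0.50 (three-group chi-square) or 0.61 (trend). The comparison of 50% with 60% alone has power 0.29 at 300 and 0.16 at 136, so the stated 0.8 cannot refer to it.

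**6. Simulation.** Beta-binomial data for 18 clusters of 28 at ICC 0.1 (40,000 runs) gave power 0.40 for the chi-square divided by the design effect and 0.34 for the cluster-level F test. A patient-level chi-square that ignores clustering rejected in 0.85 of runs, but also in 0.44 of runs with no effect, so it does not rescue the stated power.

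**7. Unequal clusters.** With DE = 1 + [(1 + CV²) × m − 1] × ICC, effective N falls to 121 at a cluster-size CV of 0.4 and 103 at 0.65. Both CVs are assumptions.

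**The case against.** The strongest reply is that the protocol does not fix the trial at 18 clusters. Population first defines eligible practices as Dutch practices using the EHR in question, and then introduces the 18 clusters with the word Initially. The sample size section does not say that the 500 patients come from those 18. With small enough clusters the step from 500 to 300 is correct arithmetic. This stands, and it makes the finding conditional. It does not rescue the figure: no later number is given, and holding N at 500, 30 clusters would give 500/2.57 = 195 and 40 would give 500/2.15 = 233. Only about 65 give 300.

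A second reply is that the shortfall in power is not all clustering. This also stands. The three-group chi-square has 0.74 at an effective 300 and needs 347 for 0.80. The fall from 0.74 to 0.39 is the part due to clustering.

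Third, the 0.33 belongs to a cluster-level F test, while the protocol names a chi-square. The section also speaks of differences per cluster. If these are changes from baseline, which the text leaves open, correlation with baseline could raise power above the figures here. That affects the power figures only, not the effective sample size statement.

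That the statistical analysis plan is not shown does not help. The protocol itself states a figure that its only cluster count contradicts.

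**Conclusion.** The figure is wrong as written for the only cluster count the protocol gives. At 18 equal clusters and an ICC of 0.1, 500 patients have an effective size of about 136, with a ceiling of 180, against the stated 300. Power is then about 0.33 to 0.49 depending on the test, and 0.39 for the three-group chi-square, against the stated 0.80. The power range rests on equal allocation, equal clusters and a post-only analysis; unequal clusters would lower it, and an analysis that uses baseline could raise it.

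A reader might go further and infer that 18 is the final number of clusters, that the correction is a plain miscalculation, and that clustering alone takes power from 0.80 to between 0.33 and 0.39. The documents do not support that. The 18 are an initial inclusion, the inputs to the correction are unstated, part of the gap comes from the choice of test, and the comparison that best reproduces the 300 gives 0.40 to 0.49.

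**What to change.** In Sample size and analysis, state the number of clusters and the mean cluster size used in the correction, and reconcile them with Population. If more than the initial 18 clusters are intended, say how many.

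Restate the figures for 18 clusters: about 28 patients per cluster, design effect 3.68, effective sample size about 136 with a ceiling of 180, and power about 0.39 for the three-group chi-square, naming the test to which the power refers. Beside this, give the number of clusters at which 300 would hold: about 65 at 7.7 patients each, or about 40 at 27.8 each (300 × 3.68/27.8 = 39.7 clusters, about 1,100 patients).

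Before data collection starts, replace the assumed ICC, 50% base rate and cluster size by values from the extraction described under Baseline measurements, and recompute with the observed variation in cluster size.

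The cost is protocol wording and a short recalculation from data the protocol already plans to extract. The downside is a much less favourable stated power. Rewording does not remove the shortfall: in 18 clusters at this ICC, more patients alone cannot bring the effective size to 300.
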